## List of abbreviations and relevant definitions

|              |                                                                                                                                                                                                               |
|--------------|---------------------------------------------------------------------------------------------------------------------------------------------------------------------------------------------------------------|
| ABR   | ABR form, General Assessment and Registration form, is the application form t that is required for submission to the accredited Ethics Committee (in Dutch: ABR = Algemene Beoordeling en Registratie) |
| AE    | Adverse Effect                                                                                                                                                                                         |
| AR    | Adverse Reaction                                                                                                                                                                                       |
| bid   | bis die (Latin): twice daily                                                                                                                                                                           |
| CRF   | Case Report Form                                                                                                                                                                                       |
| DBP   | Diastolic Blood Pressure                                                                                                                                                                               |
| DSMB  | Drug Safety Monitoring Board                                                                                                                                                                           |
| GCP   | Good Clinical Practice                                                                                                                                                                                 |
| ENT   | Equilibrative Nucleoside Transporter                                                                                                                                                                   |
| FBF   | Forearm BloodFlow                                                                                                                                                                                      |
| IR    | Ischemia-Reperfusion                                                                                                                                                                                   |
| MI    | Myocardial Infarcation                                                                                                                                                                                 |
| MR    | Mineralocorticoid Receptor                                                                                                                                                                             |
| NSAID | Non-Steroidal Anti-Inflammatory Drugs                                                                                                                                                                  |
| PORH  | Post-Occlusive Reactive Hyperemia                                                                                                                                                                      |
| (S)AE | (Serious) Adverse Event                                                                                                                                                                                |
| SBP   | Systolic Blood Pressure                                                                                                                                                                                |
| SNP   | Sodium-Nitroprusside                                                                                                                                                                                   |
| TSH   | Thyroid-Stimulating Hormone                                                                                                                                                                            |

## Summary

**Rationale:** Various studies have reported cardioprotective effects of mineralocorticoid receptor (MR) antagonists in the setting of an acute myocardial infarction. In a recent animal study, the protective effect of MR antagonists on infarct size was completely abolished in CD73 knock-out and adenosine A2b receptor knock-out mice, and by co-administration of adenosine receptor antagonists in rats. These findings suggest that extracellular formation of adenosine is crucial for this protective effect and that MR antagonists stimulate extracellular adenosine formation by the enzyme CD73.

**Objective:** To investigate whether eplerenone promotes adenosine receptor stimulation by activating CD73

**Study design:** Single center, randomized, double-blinded, placebo-controlled, cross over study

**Study population:** Twelve + 2 healthy male volunteers, aged 18-40 years

**Intervention (if applicable):** All subjects will be randomized to treatment with either eplerenone (50 mg twice daily) or a placebo. Duration of the treatment will be 8 days for both eplerenone, and placebo. After a 4-week-period the subjects will be crossed over to the other treatment group.

**Main study parameters:** A venous cannula will be inserted into the antecubital vein of the dominant arm for blood drawing. The brachial artery of the non-dominant arm will be cannulated for local drug administration. We will measure forearm blood flow (FBF) with venous occlusion plethysmography. Subsequently, the FBF response will be measured to 1) the administration of incremental dosages of dipyridamole; 2) increasing periods of arterial occlusion; 3) concomitant administration of dipyridamole and caffeine and 4) two different concentrations of both adenosine and sodium-nitroprusside.

**Primary analysis/endpoint:** FBF, pooled over the various dosages of dipyridamole, will be compared between eplerenone and placebo.

**Nature and extent of the burden and risks associated with participation, benefit and group relatedness:** A physical examination, electrocardiography and blood sampling will be performed in all participants. All subjects will be treated with eplerenone (50 mg twice daily) and placebo. Potential side effects of eplerenone include nausea, diarrhoea, constipation, hypotension, myalgia, and hyperkalemia. The chance for these side-effects to occur is limited, because the study is restricted to young healthy males with a normal renal function, and the duration of treatment will be only 8 days. We will

reduce the risk of hyperkalemia by excluding volunteers with an estimated MDRD  $<60$  mL/min/1.73 m^2 and a serum potassium  $\geq 4.8$  mmol/L. We will monitor serum potassium in the first week after start of study medication. Blood will be drawn 6 times during the study and 1 time before randomization. Volunteers will visit our clinic 9 times in total. On the four experimental days, a 27 gauge needle (outer diameter 0.4 mm) will be inserted into the brachial artery for local drug administration. This can cause a haematoma. The administration of dipyridamole, caffeine, adenosine and sodium-nitroprusside into the brachial artery has been performed many times previously by our study group, and is considered to be safe. There is no direct benefit for the participants from this study.

## 1. Introduction and rationale

Despite state-of-the-art reperfusion strategies, mortality and morbidity in patients with an acute myocardial infarction remain significant. This is caused, at least in part, by 'lethal reperfusion injury'. Therefore, novel therapeutic options to further limit ischemia-reperfusion (IR) injury are urgently needed to improve outcome in these patients.

It has been suggested that the mineralocorticoid receptor (MR) antagonists spironolactone and eplerenone could potentially serve this goal, because these drugs reduce mortality in patients with heart failure. Indeed, recent studies in murine models of myocardial infarction have shown that MR antagonists can directly limit infarct size. In more detail, in vitro studies and studies in animal models of myocardial infarction have reported that spironolactone, eplerenone, and canrenoate reduce myocardial infarction size (1-4) and protect against left ventricular remodeling (5, 6).

The underlying mechanisms of the infarct-size limiting effect are not yet fully understood, but it has been suggested that the endogenous purine nucleoside adenosine is crucially involved. In a recent animal study, canrenoate caused a dose-dependent reduction in infarct size. This protective effect of canrenoate was completely abolished in CD73 knock-out and adenosine A2b receptor knock-out mice. In rats, eplerenone significantly reduced infarct size, and this beneficial effect was abolished by co-administration of adenosine receptor antagonists. (2) These findings suggest that extracellular formation of adenosine is crucial for the protective effect of MR antagonists on IR injury.

Adenosine is an endogenous purine nucleoside, which is formed by intra-, and extracellular degradation of adenosine monophosphate by the enzyme ecto-5'-nucleotidase, which is also named CD73. Degradation of adenosine occurs in the intracellular compartment. As a consequence, facilitated diffusion of adenosine over the cellular membrane by the equilibrative nucleoside transporter (ENT) is normally directed inwards. Stimulation of membrane-bound adenosine receptors induces various effects, including vasodilation, inhibition of inflammation, and protection against IR-injury. Indeed, endogenous adenosine acts as a key mediator of the infarct size-limiting effect of several drugs.

Measurement of adenosine is extremely difficult (7), because the half life of adenosine in blood is approximately one second, due to rapid uptake and degradation. (8) Therefore,

we have used previously validated and used alternative methods to indirectly study the endogenous adenosine concentration. Dipyridamole increases the extracellular endogenous adenosine concentration by inhibition of the ENT transporter (9) and induces local vasodilation. (10) Therefore, the vasodilator effect of dipyridamole accurately reflects extracellular adenosine formation by the CD73 enzyme. (11)

Our group has recently used this method to demonstrate that statins also augment CD73 activity. Brief arterial occlusion of the forearm is an endogenous stimulus to increase adenosine formation, which subsequently enhances blood flow, resulting in so-called 'post-occlusive reactive hyperemia' (PORH). This effect is also potentiated by dipyridamole and prevented by co-administration of caffeine. (12)

In this research proposal, we aim to investigate in humans in vivo whether eplerenone promotes adenosine receptor stimulation by activating CD73. The results of these studies will provide a possible explanation for the positive effects of MR antagonists on IR-injury.

To test our hypotheses, we will use the vasodilator response in the forearm vascular bed to various stimuli as a well-validated surrogate of adenosine receptor stimulation, as will be explained in more detail in the next section.

## 2. Objectives

Primary objective:

To study whether the MR antagonist eplerenone activates CD73 and hereby increases extracellular formation of adenosine in humans in vivo, by using the forearm vasodilator response to the intrabrachial administration of the ENT-inhibitor dipyridamole.

Secondary objective:

To study whether eplerenone increases adenosine formation, by measuring forearm blood flow to incremental periods of arterial occlusion, as an endogenous stimulus for adenosine upregulation.

## 3. Study design

In this randomized placebo-controlled double-blinded cross-over study, we will test the following hypotheses:

1. Eplerenone augments the vasodilator response to dipyridamole by activation of CD73
2. The adenosine receptor antagonist caffeine attenuates this augmented vasodilator response to dipyridamole.
3. Eplerenone augments postocclusive reactive hyperemia (PORH)

We chose to use eplerenone over spironolactone, because eplerenone is a selective MR antagonist without binding to the androgen and progesterone receptor, and thus without endocrine side effects. (See also paragraph 6.4 Summary of known and potential risks and benefits)

The design of the study is depicted in figure 1. In brief, we will ask 14 healthy male volunteers (age 18-40 years) to participate. After signing for informed consent, history taking, a physical examination, blood drawing (5 mL for creatinine, potassium, ALAT, total cholesterol and glucose) and electrocardiography will be performed. We would like to refer to paragraph 4.2 and 4.3 for the in-, and exclusion criteria.

After inclusion, the volunteers will be randomly allocated to start receiving either an 8-day treatment with eplerenone or fully mimicking placebo, in a double-blinded design. The

justification of the dose and timing of administration is given in chapter 6. In the first week of treatment (on day 3, 4 or 5 –depending on the weekend-) we will monitor serum potassium by drawing 3 mL of blood, in order to guarantee the safety of treatment with eplerenone. We accept a serum potassium to 5.0 mmol/L (in contrast to 4.7 for inclusion in the study) during the study. In case of a serum potassium of  $\geq 5.1$  mmol/L, the subject will be excluded from the study and the treatment will be stopped. Two days later, serum potassium will be evaluated again.

On the 7th day of treatment, the vasodilator response to intra-arterial administration of 3 increasing dosages of dipyridamole (10, 30 and 100 ug/min/dL per forearm) will be evaluated, in the absence and presence of intra-arterial infusion of caffeine (90 ug/min per 100 mL of forearm volume). In addition, PORH to 2 incremental periods of forearm ischemia (2 and 5 minutes) will be measured. Forearm ischemia will be induced by inflation of an upper arm cuff to 200 mmHg. During a separate visit (day 8), the vasodilator responses to intra-arterially infused sodium nitroprusside (60 and 600 ng/min/dL) and adenosine (1.5 and 5.0 ug/min/dL) will be determined, to exclude non-specific effects of eplerenone on vascular reactivity and adenosine sensitivity.

Treatment duration of 8 days means administration of eplerenone or placebo twice daily during 7 days and once daily on day 8.

After this first experiment, a wash out period of 4 weeks will avoid any carry-over effect of eplerenone. After these 4 weeks, the participant will be crossed over to receive the alternative treatment arm during 8 days. Again, we will monitor serum on day 3, 4 or 5, and on day 7 and 8 exactly the same experiments will be performed.

The subjects will be studied in supine position after an overnight fast and at least 24 h of caffeine and alcohol abstinence (since caffeine is an adenosine receptor antagonist and alcohol can also affect the adenosine metabolism). Experiments are performed in a temperature-controlled room (24 °C) in the morning after an overnight fast. At the start of the experiment, we will insert a venous cannula into the antecubital vein of the dominant arm for blood drawing. Blood will be drawn before start of each experiment: 20.5 mL on

day 7 for the determination of the serum potassium, sodium, creatinine, plasma caffeine (to check compliance with caffeine abstinence), aldosterone, renin, and eplerenone concentration; and 3 mL on day 8 for the determination of plasma caffeine only. Subjects with a circulating caffeine concentration > 1.0 mg/l will be excluded from analyses. Twenty-four hours urine samples will be collected and sodium and creatinine will be determined, to ensure that salt intake is approximately the same during both treatment days.

Study medication will be taken under supervision of the researcher. One hour after ingestion of the drug, a 27-gauge needle (B. Braun Medical B.V.) will be inserted into the brachial artery of the non-dominant arm for intra-arterial drug administration. The outer diameter of this needle is 0.4 mm. In both arms, forearm blood flow (FBF) will be measured simultaneously with venous occlusion plethysmography, using mercury-in-silastic-strain gauges and occluded hand circulation as described previously. (12) Thirty minutes after cannulation of the brachial artery, normal saline is infused with concomitant measurement of baseline FBF for 5 min.

So, approximately 1.5 hours after ingestion of the study medication, the experiment will be started and FBF will be measured around the  $T_{\max}$  of eplerenone (approximately 2 hours) Three experiments will be performed, which are all separated by 30 minutes of wash-out.

1. FBF will be measured during the administration of increasing dosages of dipyridamole into the brachial artery. These dosages are similar to a previous study of our group. (10) We hypothesize that in patients treated with eplerenone, the dipyridamole-induced vasodilation is potentiated due to upregulation of CD73.
2. Subsequently, we will measure the vasodilator response to 2 incremental periods of arterial occlusion ('post-occlusive reactive hyperemia'). Forearm ischemia will be induced by inflation of an upper arm cuff to 200 mmHg, as described previously. (11) We have previously demonstrated that the PORH after 2 and 5 minutes of ischemia is potentiated by statins (by increasing the extracellular formation of adenosine) (11) and by dipyridamole (by inhibition of the ENT transporter). (12)

3. We will finish the experiment on day 7 with measurement of FBF during the concomitant administration of the three increasing dosages of dipyridamole and of caffeine (90 ug/min per 100 mL of forearm volume) into the brachial artery.
4. Finally, on day 8, we will record the forearm vasodilator response to the administration of adenosine (1.5 and 5.0 ug/min/dL) and SNP (60 and 600 ng/min/dL) to exclude non-specific effects of eplerenone on vascular function and adenosine sensitivity.

Furthermore, we will measure blood pressure at baseline and during the experiments, on day 7 and 8, in all volunteers.

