#### 4.4. Sample size calculation (performed by [name], dept. of Health Evidence)

Based on earlier, similar studies with a parallel groups design, we expect that the standard deviation of the logarithm of the FBF will be approx. 0.35 and that the correlations between the measurements within each period of the cross-over will be approx. 0.7. (12, 13) Based on these assumptions and a difference of 25% between the groups, the analysis described in the statistical section of the protocol, carried out on two parallel groups of 12 subjects, is expected to have approximately 80% power (two-sided testing at 0.05; the design factor for a pooled analysis on k follow-up measurements adjusted for baseline is  $\frac{1}{k} + k \cdot \frac{1}{k} \rho - \rho^2$ ). The proposed study is a cross-over trial, so the power of a 12-subject-study may be higher, as the subjects serve as their own control. However, this is to some extent also the case in a parallel study, because the baseline is included as a covariate in the analysis. Hence, the power of a cross over study with 12 evaluable subjects is expected to be only marginally higher than 80%. In order to have 12 evaluable subjects, we will enroll 14 subjects. (see also paragraph 8.5)

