### 10.2 Secondary study parameter(s)

The reduction in FBF response, due to the administration of caffeine in the presence of dipyridamole and eplerenone, will be analysed in a similar way, using a linear mixed-model analysis with random factor subject, fixed factors dipyramole dose, caffeine (yes/no), dipyramole dose \* caffeine, and period. The logarithm of the baseline FBF will be included as co-variables. The dependent variable will be the log-transformed FBF after eplerenone administration (with and without caffeine). Other endpoints will be analysed using similar random effects models. A p-value of  $< 0.05$  will be considered to be statistically significant.

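### The adenosine and nitroprusside responses are meant to exclude non-specific effects, but the only rule that reaches them is a difference test at p<0.05, which with 12 subjects cannot do that by itself

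*Protocol*

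**What the plan says.** Hypothesis 1 in Section 3 (Study design) is mechanistic: eplerenone increases the dipyridamole response through CD73. Section 3 describes the day-8 infusions twice, once as serving "to exclude non-specific effects of eplerenone on vascular reactivity and adenosine sensitivity" and once as serving "to exclude non-specific effects of eplerenone on vascular function and adenosine sensitivity". Each agent is given at two dose levels: "adenosine (1.5 and 5.0 ug/min/dL) and SNP (60 and 600 ng/min/dL").

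Section 10.1 covers dipyridamole and 10.2 the caffeine comparison. Everything else falls under one sentence in 10.2: "Other endpoints will be analysed using similar random effects models". The next sentence there says that a p-value below 0.05 "will be considered to be statistically significant". No margin, precision target or interpretation rule is given for the two controls.

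Section 8.1.2 lists dipyridamole with and without caffeine, and arterial occlusion. Sections 8.1.3 and 10.3 are marked not applicable. The Summary does name the adenosine and SNP responses among the main study parameters. The sample size in 4.4 is derived for the pooled dipyridamole analysis only.

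**The concern.** A larger dipyridamole response under eplerenone has at least three explanations: more extracellular adenosine, greater sensitivity to adenosine, or greater vasodilator reactivity in general. The primary test cannot tell them apart. The caffeine experiment shows dependence on adenosine receptors but does not separate more adenosine from greater sensitivity to it. Only the adenosine and SNP responses address the second and third explanations, so the specificity claim rests on them.

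Excluding an effect is a claim that any effect is too small to matter. A difference test that fails to reject does not support it unless the estimate is precise enough. If a non-specific gain of 15% or 20% can easily go undetected, much of a 25% dipyridamole effect could be non-specific while both controls look clean.

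**Working it through.** **Inputs.** From 4.4: "the standard deviation of the logarithm of the FBF will be approx. 0.35", correlation 0.7 within a period, a 25% difference (log 1.25 = 0.2231), "two-sided testing at 0.05", and 12 evaluable subjects. From Section 3: k = 3 doses of dipyridamole and k = 2 of each control agent. The between-period correlation r is not in the protocol; I assume 0 to 0.7.

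**The plan's own figure.** Section 4.4 says the analysis, on two parallel groups of 12, "is expected to have approximately 80% power". The design factor is not cleanly legible in the text at hand; I read it as 1/k + ((k−1)/k)ρ − ρ².
- k = 3: 0.333 + 0.467 − 0.49 = 0.31. Adjusted SD = 0.35√0.31 = 0.1949; SE = 0.1949√(2/12) = 0.0796. Power = Φ(0.2231/0.0796 − 1.96) = 80.1%, so the figure is reproduced.
- k = 2 (one control agent): 0.5 + 0.35 − 0.49 = 0.36. Adjusted SD = 0.21; SE = 0.0857. Power for the same 25% effect is 74%. A true effect is non-significant in 63% of trials at 15%, 43% at 20% and 26% at 25%.

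**The cross-over.** The mean of two doses has variance factor (1 + 0.7)/2 = 0.85. The baseline-adjusted within-subject difference has variance 0.35²·v, with v = 2[(0.85 − r) − (0.7 − r)²/(1 − r)] and SE = 0.35√(v/12). At r = 0, v = 2 × 0.36, which is the plan's parallel-group factor. Miss probabilities use the noncentral t with 9 df (12 differences less mean, period and baseline terms; critical value 2.262). The CI factor is exp(2.262·SE).

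| r (assumed) | v | SE | 95% CI factor | 15% missed | 20% missed | 25% missed |
|---|---|---|---|---|---|---|
| 0 | 0.72 | 0.0857 | 1.21 | 69% | 52% | 36% |
| 0.6 | 0.45 | 0.0678 | 1.17 | 55% | 33% | 17% |
| 0.7 | 0.30 | 0.0553 | 1.13 | 39% | 17% | 5% |

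A just non-significant increase has an upper 95% limit equal to the CI factor squared: about 1.47, 1.36 and 1.28. All exceed 1.25.

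**A gain common to both agents.** Here both tests must miss. With an equal gain on both agents, and 0.7 also taken as the within-period correlation between agents, both miss in 55% to 35% of trials at 15% and in 36% to 15% at 20% (r = 0 to 0.6). At r = 0.7 the two estimates are uncorrelated in this model, so the figures are about 0.39² = 15% and 0.17² = 3%.

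**Equivalence margins.** With no true effect, the chance that a 90% CI lies within 1/m to m is about 2Φ(ln m/SE − 1.645) − 1, or 0 if negative. Over SE 0.0857 to 0.0553 this is 0% to 62% for m = 1.15 and 0% to 6% for m = 1.10. For 0.80–1.25, the t-based figure is 56% to 83% per agent and 36% to 71% for both (r = 0 to 0.6). With a true 15% non-specific gain, that same margin would still be met in about 22% to 31% of trials per agent.

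**The case against.** The strongest reply is that the protocol never says how a null control result will be interpreted. The verb exclude may state only the purpose of a control infusion, much as 4.1 uses it for enrolling men only. The p<0.05 rule reaches the controls only through a general sentence. Margins and contrasts for supporting experiments often sit in a statistical analysis plan. The Summary does name these responses, and 10.1 promises 95% CIs for the primary analysis, which similar models could also supply for the controls.

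Much of this stands. A reader might infer that a non-significant result will be presented as proof of specificity; the text does not say so. A reader might also infer that a general gain in reactivity would usually go unnoticed. That is too strong: in the model above both agents miss more often than not only for a 15% gain with low between-period correlation. The responses are also not undeclared, since the Summary lists them. The single-agent risk applies in full to a change in adenosine sensitivity alone.

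What the reply does not remove is the mismatch within the protocol. It assigns these data the task of exclusion, and the one rule that covers them tests for a difference. A statistical analysis plan may add a margin, but the protocol's stated rule would still not serve its stated purpose.

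**Conclusion.** The point holds in this form: the stated purpose needs evidence that any non-specific effect is small, and the only rule given cannot provide it by non-significance alone. Per agent, a 15% effect is missed in about 69% to 39% of trials and a 20% effect in about 52% to 17%. These figures rest on the plan's SD and correlation applying to the day-8 data, 12 evaluable subjects, and an assumed between-period correlation of 0 to 0.7; a higher one would improve them. An estimate near 1 with a tight interval could rule out a 25% effect, so it is the reliance on the p-value that fails, not the experiment. The primary test is unaffected; its CD73 interpretation is what is exposed.

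**What to change.** 1. List the adenosine and SNP responses in 8.1.2.
2. In 10.2, test directly, in the same mixed model, whether the eplerenone/placebo log ratio for dipyridamole exceeds that for adenosine and that for SNP. This addresses specificity without relying on a null result.
3. Report each control ratio with its 95% CI. State that a non-significant control will not be taken as exclusion, that the report will name the size of non-specific effect the interval rules out, and that otherwise it will say *not excluded*.
4. If an equivalence margin is used, justify one clearly smaller than the 25% target. A 0.80–1.25 margin would equal the whole target effect.

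This needs no extra subjects, visits or procedures. The cost is a more cautious claim: with 12 subjects a 10% margin would almost never be met and a 15% margin only if the between-period correlation is high, so the specificity statement may often have to be softened even if the effect is truly specific. The direct contrasts also have limited precision, which should be reported with them.
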